## 7. Arrhythmias

Serious Adverse Events/Deaths will be reported separately in a similar fashion to the more general AE reports. In addition, narratives will be available for each event.

The analysis of safety outcomes will be undertaken as detailed below:

1. **Frequency of diarrheal episodes during the 48-hours following ED disposition:** The total number of episodes of diarrhea related to the presenting illness will be compared between groups (active and placebo) using a generalized linear model to compare differences between Poisson rates whilst adjusting for stratification.
2. **Maximal number of diarrheal episodes in 24 hours:** To test whether this outcome differs between the active and placebo treatments, we will use a Mann-Whitney U-test.
3. **Serious Adverse Events (SAEs):** The frequency of SAEs will be reported for both active and placebo groups. No formal testing will be undertaken.
4. **Palpitations:** The frequency of palpitations will be reported for both active and placebo groups. No formal testing will be undertaken.
5. **Pre-syncope /syncope:** The frequency of pre-syncope/syncope will be reported for both active and placebo groups. No formal testing will be undertaken.
6. **Chest Pain:** The frequency of chest pain will be reported for both active and placebo groups. No formal testing will be undertaken.
7. **Arrhythmias:** The frequency of arrhythmias will be reported for both active and placebo groups. No formal testing will be undertaken

---

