## 4 STUDY DESIGN

### 4.1 OVERALL DESIGN

We will conduct a Phase III multi-centre, 2-arm, placebo-controlled, double-blind, parallel design randomized controlled trial comparing the effectiveness and adverse event profile of multiple dose (as needed) oral ondansetron compared with placebo when administered to children with acute gastroenteritis (AGE)-associated

vomiting following ED discharge. The study will be stratified by site (6 sites) and weight (< 20kgs and ≥ 20kgs). Weight is being employed, rather than age, as dosing is weight based.

We hypothesize that the administration of ondansetron post-ED discharge will be associated with improved outcomes as compared with placebo.

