## 8 STUDY ASSESSMENTS AND PROCEDURES

### 8.1 EFFICACY ASSESSMENTS

Primary and secondary endpoints will be determined by the outcome measures. Assessments performed will support the outcome measures listed in Section 3.0 Objectives and Endpoints.

**Screening:** Participants presenting to the ED of a participating institution will be screened for eligibility using the eligibility criteria listed in sections 5.1 and 5.2 by a trained research team member. The research team member will ask the caregiver questions related to the patient's medical history and current medications that may be contraindicated. Inclusion/exclusion criteria will be determined based on caregiver report of patient's medical history and the details of their current illness. This information will be confirmed with the treating physician to ensure accuracy of reported information and medical oversight. In addition to the patient's medical history, eligibility depends on the treating physician ordering at least 1 dose of ondansetron while the patient is still in the ED, as well as the patient's ED diagnosis. This information will be confirmed using physician or nursing orders and the patient's ED medical chart by the research team member. Permission to access the patient's chart for screening purposes will be obtained from the caregiver/legally authorized individual, in accordance with provincial access to health information legislation.

**Enrollment/Baseline Assessments (outcome assessment):** A baseline questionnaire will be performed to obtain information supporting the study's outcome measures (e.g. *current medical history, duration and frequency of vomiting, presence of fever, duration and frequency of diarrhea, satisfaction scale, etc.*).

In addition to the questionnaire listed above, the trained research team member will obtain the participant's heart rate (HR) and respiratory rate (RR) at the Enrollment/Baseline visit. The triage temperature and weight will be obtained from the ED medical record. To obtain a baseline understanding of the participant's health and medical condition, a basic review of systems and concomitant medications will also be performed.

**Follow-up:** Outcome measure end-point data will be obtained using follow-up questionnaires performed 24, 48, and 168 hours (7 days) after the Baseline/Enrollment visit Time 0 (Consent date and time) by research study staff. Questions will be asked related to the following:

- Frequency and duration of vomiting

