6. **Unscheduled healthcare visit:** Presence of an unscheduled healthcare visit will be collected on the questionnaire and will be classified as “none”, “primary care”, or “emergency department”. All revisits to the participating site are verified by database review.
7. **Treatment:** Treatment will be classified as “none”, “intravenous rehydration”, or “hospital admission”. If the participant is admitted directly following their enrollment ED visit and that admission stay is longer than 48 hours, it will be counted as treatment in the post enrollment MVS. If the participant’s enrollment admission stay was less than 48 hours, it will not be counted as “treatment”.

Data needed to calculate the MVS will be collected at Enrollment (Day 0), on the 24, 48, and 168 hour questionnaires, and verified using chart review performed within 37 days of participant enrollment. The primary outcome will be tabulated by treatment for each site and weight stratum. A Mantel-Haenszel statistic, assessing the effect of treatment on the primary outcome controlling for strata, will be calculated to test the primary hypothesis. Summary statistics for the effect sizes will be given. Choice of final summary statistic reported (e.g. risk difference, risk ratio, or odds ratio) will be based, in part, by which statistic is least variable across subgroups (i.e. shows the smallest degree of interaction across subgroups). It is expected that the asymptotic version of the Mantel-Haenszel test will be appropriate for the final analysis. In the case of low outcome counts, the Mantel-Fleiss criterion will be assessed. If the criterion has a value less than 5, the exact version of the Mantel-Haenszel test will be used and the two-sided p-value will be defined as the sum of all probabilities of test statistics with point probabilities less than or equal to that of the observed value. In the event any patients were randomized within an incorrect stratum due to misspecification at time of randomization, the actual, rather than assigned category will be used in the above analysis.

Although randomization should result in approximate balance between treatment arms with respect to critical baseline variables affecting the outcomes, additional exploratory analyses will be conducted to assess the effects of treatment after adjusting for baseline covariates in models for the primary outcome.

The covariates considered are:

- Baseline MVS (actual score)

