- Duration of symptoms prior to enrollment (<48 hours vs. 48 hours or more)
- Age
- Gender
- Clinical center

- Antibiotic usage during the 14 days prior to ED visit
- Severity of baseline diarrhea and vomiting
- Hydration assessment
- Need for hospitalization at index visit

---

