5. **Proportion of participants who require intravenous rehydration:** If the participant required an unscheduled health care visit (see #4 above), the participant will be asked additional questions related to intravenous (IV) insertion, treatment course, and disposition. Intravenous fluids administered at the index visit will not be included as part of this outcome.
6. **Caregiver satisfaction as measured by a 5-point Likert scale in the 48 hours following ED disposition:** Caregiver satisfaction with the therapy provided (oral ondansetron or placebo) in the 48 hours following ED disposition. This will be measured using a 5 point Likert scale on the questionnaire administered 168 hours after Time 0.

The analysis of secondary outcomes will be undertaken as detailed below:

1. **Frequency of vomiting from study enrollment to Day 7:** The total number of episodes of vomiting and diarrhea related to the presenting illness will be compared between groups (active and placebo) using a generalized linear model to compare differences between Poisson rates whilst adjusting for stratification.

2. **Duration of vomiting :** The total number of days the participant experiences vomiting from Day 0 to Day 7 will be compared using the Van Elteren test, stratified by center and duration of symptoms (pre-enrollment). If a number of patients still experience symptoms at the 7-day follow-up questionnaire, this will be tested using a suitable procedure to take account of censoring such as median regression or additive hazard models. Additional analyses involving this outcome will include linear regression models that adjust for possible effects of baseline characteristics.
3. **Proportion of participants who experience vomiting within 7 days of enrollment:** The proportion of participants with vomiting following enrollment will be compared using Mantel-Haenszel test stratified by site and weight.
4. **Proportion of participants who require an unscheduled health care provider visit within 7 days of enrollment:** The proportion of participants who require an unscheduled health care provider visit within 7 days of enrollment will be compared using Mantel-Haenszel test stratified by site and weight.

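### The 48-hour diarrhea count and the vomiting count are adjusted for site and weight only, so precision that the collected baseline symptom counts could give is lost and a chance baseline imbalance goes uncorrected

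*Combined protocol and SAP*

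**What the plan says.** Section 9.4.4, analysis item 1, states that the 48-hour diarrhea count "will be compared between groups (active and placebo) using a generalized linear model to compare differences between Poisson rates whilst adjusting for stratification". Section 9.4.3, analysis item 1, compares the Day 0 to Day 7 vomiting frequency "using a generalized linear model to compare differences between Poisson rates whilst adjusting for stratification".

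The stratification factors are given in section 4.1: "The study will be stratified by site (6 sites) and weight". Section 6.3 repeats them. Neither is a symptom variable.

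Baseline symptoms are available. The enrolment questionnaire in section 8.1 covers "duration and frequency of vomiting, presence of fever, duration and frequency of diarrhea". Section 9.4.1 reports them by arm. The baseline Modified Vesikari Score also needs a maximum 24-hour count of stools and of vomits (Table 3.0).

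The plan uses baseline symptoms as covariates, but for other outcomes:

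- Section 9.4.2 says that "additional exploratory analyses will be conducted to assess the effects of treatment after adjusting for baseline covariates in models for the primary outcome" and lists "Severity of baseline diarrhea and vomiting" among the covariates.
- For vomiting duration, section 9.4.3 adds: "Additional analyses involving this outcome will include linear regression models that adjust for possible effects of baseline characteristics".
- Section 9.4.7 uses baseline vomiting frequency and presence of diarrhea as subgroup factors for the primary outcome.

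No main, additional or sensitivity analysis of either count includes the child's own baseline count.

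**The concern.** Entry requires vomiting, not diarrhea (section 5.1), so children with and without diarrhea at enrolment enter the same 48-hour stool comparison. Baseline diarrhea plausibly predicts later stools. Leaving it out puts predictable between-child variation into the error term, and a chance difference between arms in the share with diarrhea carries straight into the estimate.

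This matters most for diarrhea. Section 4.2 says that any benefit has to be weighed against more frequent diarrhea, and the 48-hour count is the first safety endpoint in Table 1.0. Vomiting and diarrhea frequency also sit in the Holm family of section 9.4.1, where the first threshold is 0.05/8, so precision has value there too.

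**Working it through.** **The plan's own figures.** The documents give no power or precision for either count. The only sample size is for the binary primary outcome. For 30% against 20%, two-sided 0.05 and 90% power: n per arm = [1.96 × √(2 × 0.25 × 0.75) + 1.2816 × √(0.3 × 0.7 + 0.2 × 0.8)]² / 0.10² = 392, total 784, as stated in section 9.2.

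**Number analysed.** 1030 randomised less 10% loss is 927, or about 464 per arm. Section 9.3 limits the safety set to children who took a dose, and section 6.4 counts zero doses as compliant, so the diarrhea analysis may have fewer.

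**Assumed inputs (not in the documents).** p is the share with baseline diarrhea. m1 and m0 are the mean 48-hour stools with and without it. Counts are negative binomial with variance m + m²/k.

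- Between-group variance: B = p(1−p)(m1−m0)²
- Within-group variance: W = p(m1 + m1²/k) + (1−p)(m0 + m0²/k)
- R² = B/(B+W)
- SE cut = 1 − √(1−R²)
- Equivalent extra patients = 1/(1−R²) − 1
- SE of the unadjusted mean difference = √(2(B+W)/464)
- Shift from a 1.96-SD imbalance = 1.96 × √(2p(1−p)/464) × (m1−m0)

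| | A: p 0.5; 6 vs 1; k 1.0 | B: p 0.5; 5 vs 1.5; k 0.7 | C: p 0.4; 5 vs 2; k 0.7 |
|---|---|---|---|
| B / (B+W) | 6.25/28.25 | 3.06/25.78 | 2.16/23.07 |
| R² | 0.221 | 0.119 | 0.094 |
| SE cut | 11.8% | 6.1% | 4.8% |
| Extra patients | 28% | 13% | 10% |
| Imbalance (points) | 6.4 | 6.4 | 6.3 |
| Shift (stools) | 0.32 | 0.23 | 0.19 |
| Shift as % of overall mean | 9% | 7% | 6% |
| Unadjusted SE | 0.349 | 0.333 | 0.315 |
| Shift in SE | 0.92 | 0.68 | 0.60 |

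The extra-patient figure is 1/(1−R²) − 1, not R² itself. For scale, one earlier trial in section 2.2 reported 5.0 against 4.3 diarrheal episodes, an excess of 0.7/4.3 = 16%.

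**Dependence on the correlation r.** The SE cut is 1 − √(1−r²), and the shift in SE units is 1.96r.

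| r (assumed) | SE cut | Extra children on 927 | Shift at 1.96-SD imbalance |
|---|---|---|---|
| 0.2 | 2.0% | 39 | 0.39 SE |
| 0.3 | 4.6% | 92 | 0.59 SE |
| 0.4 | 8.3% | 177 | 0.78 SE |
| 0.5 | 13.4% | 309 | 0.98 SE |
| 0.6 | 20% | 521 | 1.18 SE |

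**Simulation.** Setup: 926 children, 12 strata, assumed mean of 3.5 episodes, overdispersed counts, resulting r of 0.21-0.47, 700-1000 runs per scenario, robust SE.

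- No effect: overall type I error was 4.6-6.1% with strata only and 5.1-6.6% with baseline added.
- The SD of the log rate ratio with baseline added was 0.88-0.98 of the strata-only SD.
- True rate ratio 1.25: power rose from 56% to 63% (r 0.36) and from 41% to 51% (r 0.44).
- Null trials with a chance imbalance beyond 1.5 SD and r of 0.36-0.47 (399 runs pooled): false positives were about 13.5% with strata only and about 6% adjusted. At r of 0.21 they were 5.8% and 4.2% (120 runs).
- With plain Poisson standard errors, false positives were 39-60% with strata only and still 34-56% with baseline added.

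**The case against.** A strata-adjusted comparison of randomised arms is valid without baseline covariates, and its confidence interval already allows for chance imbalance. This stands. A reader might infer that the planned analysis is biased or inflates type I error; neither the documents nor the simulation support that. Nor could the imbalance in scenarios A-C create significance by itself: the shift is 0.19-0.32 stools against a 95% half-width of 0.62-0.68 (1.96 × SE). The raised false-positive rate applies only to trials that happen to have a sizeable imbalance.

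The inputs are assumed. This also stands. Prevalence of baseline diarrhea, stool means and dispersion appear nowhere in the documents, and nothing there shows baseline diarrhea to be the strongest predictor.

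The argument from a mixed sample does not carry over to vomiting, since every child must have vomited at least three times in the preceding 24 hours (section 5.1). Baseline frequency still varies among them, but a reader should not infer a similar loss for that endpoint: no figure supports it.

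The plan offers partial mitigation. Baseline tables by arm would reveal an imbalance, section 6.3 expects stratification to spread pathogens and practice patterns evenly, and labelled post hoc analyses are allowed (section 9.4.9). None of this prespecifies adjustment of the counts, and deciding to adjust after seeing an imbalance is what prespecification avoids.

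Finally, the safety set is chosen after randomisation by caregiver dosing, so the assurance about randomised arms carries over to it less surely. The documents do not say how many children it will hold or whether the arms will differ in it.

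**Conclusion.** The point holds as a weakness in precision and in handling chance imbalance, not as an error in the test. Under the assumed inputs, baseline diarrhea explains about 9-22% of the variance in 48-hour stools. Leaving it out costs what 10-28% more patients would buy, and an imbalance at the edge of the 95% range leaves 0.6-0.9 SE in the estimate. The loss is negligible near r = 0.2 and material from about r = 0.4. The text is clear that the adjustment is absent; how much it matters is uncertain. The case is strongest for the diarrhea count. For vomiting it rests only on the adjustment being free. A reader might also infer that adding baseline counts would make the Poisson models sound. It would not: the false-positive rates under plain Poisson errors hardly improve, so overdispersion needs its own remedy.

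**What to change.** In section 9.4.4, item 1, add baseline diarrhea presence and baseline 24-hour stool count to the model. In section 9.4.3, item 1, add the baseline 24-hour vomiting count, as a lesser addition with no gain quantified. State which baseline 24-hour figure is meant (for example, the maximum used in the baseline score or the preceding 24 hours). Keep site and weight in both models. Report the adjusted rate ratio with its 95% confidence interval, and keep the strata-only model as a sensitivity analysis. With a log link the rate ratio is collapsible, so if the effect does not vary with baseline the adjusted ratio has the same meaning.

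The cost is about one line per model, fixed before unblinding, with no new data collection. Separately, specify a robust or negative-binomial variance for both counts; neither change replaces the other.

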### 9.4.5 BASELINE DESCRIPTIVE STATISTICS

Baseline characteristics will be compared between groups using frequency counts and percentages for discrete variables, and means, medians, standard deviations, and interquartile ranges for continuous variables.

---

### 9.4.6 PLANNED INTERIM ANALYSES

As per the DSMB charter, no interim analysis will be performed for the DOSE-AGE study. In the case that an interim analysis is to take place, it will be done in accordance with the DSMB charter. We will also make the appropriate adjustments to the significance level and update the study Statistical Analysis Plan.

Early stopping for efficacy and futility will not be considered due to concerns for overestimating or underestimating treatment effects. The DSMB will, in collaboration with the trial steering committee, establish safety stopping rules prior to trial initiation.

Data center biostatisticians involved in this study will be partially blinded, aware of results by treatment arm, but not of arm identities. Other data center personnel will be blinded to treatment assignments, however the data center study team for this trial will have access to individual safety and efficacy data. Personnel at the clinical centers will be blinded to aggregate safety and efficacy data until the time of final analysis or until the decision is made to unblind all investigators to study results.

All by-treatment interim analyses will refer to arms as “A” and “B” throughout the report presented to the DSMB. The DSMB will have the option of being unblinded to treatment arm identity at any time.

For additional information about safety stopping rules, reference the DSMB charter.

---

#### 9.4.7 SUB-GROUP ANALYSES

The following pre-specified subgroup analyses of the primary outcome will be performed:

1. Sex
2. Age: 6 months to 3 years; 3 to 6 years; 6 to 10 years; >10 years
3. Vomiting frequency: >10 episodes in preceding 24 hours
4. Presence of diarrhea (yes/no) in preceding 24 hours

A “subgroup” effect will be declared to be significant only if the interaction between assigned treatment and the subgroup factor is significant in the appropriate statistical model testing for each particular interaction, at a significance level of  $0.05/4 = 0.0125$ . These results must still be viewed with caution given the number of subgroup analyses. As the primary outcome is binary, logistic regression models will be used with a main effect for treatment, a main effect for the subgroup variable of interest, and an interaction between the subgroup variable of interest and the treatment. We will also consider stratifying by site and weight in subgroup analyses.

---

#### 9.4.8 TABULATION OF INDIVIDUAL PARTICIPANT DATA

In the analyses planned, no individual participant data will be listed.

---

#### 9.4.9 EXPLORATORY ANALYSES

The final analysis for the comparison of oral ondansetron to placebo will take place in one stage. The main report of the trial will be prepared after every participant has completed the protocol and all data has been collected, cleaned, and the database has been “closed”.

Any post hoc, exploratory analyses completed to support planned study analyses, which were not identified in the study SAP, will be documented and reported as such in all study publications.

---

## 10 SUPPORTING DOCUMENTATION AND OPERATIONAL CONSIDERATIONS

---

### 10.1 REGULATORY, ETHICAL, AND STUDY OVERSIGHT CONSIDERATIONS

---

#### 10.1.1 INFORMED CONSENT PROCESS

---

##### 10.1.1.1 CONSENT/ASSENT AND OTHER INFORMATIONAL DOCUMENTS PROVIDED TO PARTICIPANTS

Consent forms describing in detail the study intervention, study procedures, and risks are given to the caregiver or legally authorized representative (LAR) for the participant, and all participants beyond age of maturity. The consent process will be completed by a trained study team member. Written documentation of informed consent is required before collecting any data (with the exception of data related to eligibility determination), performing study procedures, or randomization to the study intervention.

In accordance with TCPS2: Tri Council Policy statement regarding consent of minors, consent from mature minors will be sought where applicable. The age of consent varies by province however if the age of consent has been reached, consent will be obtained from the participant directly, provided the research team deems the individual to have decision making capacity (section 10.1.1.2). Due to the large amount of communication and symptom tracking required, caregivers of mature minors will also be required to provide informed consent for completion of the study questionnaires, where mature minor consent is applicable.

Assent forms describing in detail the study intervention, study procedures, and risks will be provided to participants who are the age of assent. The age of assent will be defined by local REB policy, as outlined by ICH-GCP E11 'Clinical Investigations of Medicinal Products in the Pediatric Population' (*e.g. the University of Calgary REB requires assent be obtained from children age 7 years and older*).

Written documentation of informed consent is required before randomizing to/administering study intervention. Assent reading level will be determined based on REB guidelines at each participating study site (*e.g. University of Calgary REB Assent Requirements: children aged 7-11 years = reading level of grade 2; children 12 years and older = reading level of grade 4*).

All caregiver and mature minor informed consent forms should be written at a grade 6-8 reading level.

The trained research team member will review the applicable consent/assent forms with the caregiver/LAR and participant and provide them with a copy for independent review. The consent process will be documented by the research team member obtaining consent.

---

